##### Sample size

The primary objectives of the study are to develop a model to discriminate between patients with and without symptomatic TE. To determine the optimal discriminant clinical model we will undertake a multivariable analysis. Simulation studies demonstrate that logistic models require 10 to 15 events per predictor to produce stable model estimates [54,55]. Based on our retrospective data and published reports we anticipate that at least 20% patients will be exposed (i.e. with CVL dysfunction) and 80% unexposed (i.e. without CVL dysfunction) [17,33,36]. Preliminary data from the retrospective study showed that the overall prevalence of TE was 11%; 23% of exposed and 9% of unexposed patients had TE. We will evaluate five predictors in our multivariable analysis. In this study, we have a fixed sample size of 450 patients (90 exposed with CVL dysfunction; and 360 without CVL dysfunction). The overall rate of symptomatic TE is assumed to be 11% (~50 events of TE) [36].

## Discussion

To our knowledge, this is the first prospective and comprehensive evaluation of CVL-dysfunction in pediatric oncology. This study will improve our knowledge regarding the mechanism of CVL-dysfunction and the relationship amongst CVL-dysfunction, infection and TE in children with cancer. Most importantly this study will evaluate the impact of CVL-dysfunction on the development of TE, infection and overall outcome from cancer in children.

TE is a growing and significant problem in children with cancer. TE can be treated with anticoagulant therapy. Hence it is important to have reliable methods for early diagnosis of TE. In addition, TE is preventable with anticoagulant prophylaxis [13,14]. However, children with cancer are also at risk of bleeding from thrombocytopenia and other effects of treatment. Children with cancer receiving anticoagulation therapy or prophylaxis are shown to have 5-15% bleeding risk [9,10,56]. Ideally, thromboprophylaxis is offered only to those patients with high risk of thrombosis and low or acceptable risk of bleeding. Thus, for judicious use of thromboprophylaxis, identifying a population at high risk for TE is of paramount importance. The proposed study aims to identify predictors of TE in children with cancer.

If we confirm our primary hypothesis then we can use CVL-dysfunction as a predictor of TE and will be able to identify children at high risk for TE. Based on the results of this study we will design future studies for earlier diagnosis of TE using definitive methods like venography and future randomized controlled trial of prophylactic anticoagulant therapy in children with cancer. This will ultimately help to reduce the incidence of TE and its impact on overall outcome as well as quality of life in children undergoing treatment for cancer.

If we confirm the association of CVL-dysfunction, TE and infection, then we can identify children at high risk for infection (a major complication in children with cancer) and institute prophylactic strategies aimed at reducing dysfunction and infection (e.g. anticoagulation therapy).

In addition, this study will compare the practices of CVL insertion and care across five pediatric tertiary care centers in Ontario. Although each institution has based their practices on internal quality control studies, there are so far no data comparing or evaluating different practices across the Province in large patient population. This study will allow us to evaluate the impact of institutional practices of CVL insertion and care on the development of CVL-related complications. This will help to develop evidenced based guidelines for CVL insertion and care.

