### Study rationale

#### Rationale for primary aim

CVL-related TE in children is difficult to diagnose. CVL-related TE could be symptomatic (with pain, edema, skin discoloration and dilated veins) or asymptomatic [37,38]. The presence of symptoms reflects the site of obstruction, size of obstruction and acuteness of obstruction. In children, especially in younger age group, the symptoms of TE are difficult to detect. Hence even a significant TE may go un-noticed. Journeycake et al., showed that only 5 of 21 children with CVL-related TE were symptomatic; 10 of 16 “asymptomatic” children had multiple CVL placements prior to the diagnoses of TE [17]. This observation highlights the importance of a reliable screening method for diagnosis of CVL-related TE.

Although compression ultrasonography (USG) is the diagnostic test of choice for suspected lower venous system deep venous thrombosis (DVT), it has poor sensitivity for the diagnosis of DVT in the upper venous system (central subclavian vein, brachiocephalic and superior vena cava) [37,38]. Within the thoracic cage, the non-compressibility of the vessel cannot be assessed due to the bony ribs [39]. Prospective studies have shown that bilateral venography is the most sensitive technique for diagnosis of upper venous system TE within the thoracic cage [37-40]. However, venography is an invasive, cumbersome and painful procedure, and it exposes children to excessive radiation. Hence venography cannot be used as a routine screening tool for evaluation of CVL-related TE in children with cancer. Magnetic resonance venography (MRV) is another non-invasive, safe and reliable method to diagnose DVT. Although safe, MRV is very costly, requires sedation or general anesthesia for younger patients making it unsuitable for screening purposes, and its sensitivity and specificity in children have not been well defined [40]. Further, CVL-related small clots such as fibrin sheath or ball valve thrombi (which are mostly responsible for CVL-dysfunction) may not be detected by USG or even linogram.

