Thus, there is no reliable, safe, inexpensive and noninvasive screening tool for diagnosis of CVL-related TE in children. Hence one may have to consider surrogate markers as predictors of underlying TE. An ideal predictor will reliably identify patients with high a probability of underlying TE for whom evaluation by invasive tests will be justified. Considering available evidence, we propose that CVL-dysfunction may be a good predictor of underlying TE. If indeed the presence of CVL-dysfunction can predict TE then such patients could be evaluated further with the gold standard test of venography and treated with anticoagulation therapy. This in turn will reduce the risk of development of symptomatic TE and infection. However, the first step is to confirm the presence (and the strength) of association of CVL-dysfunction and TE in a large prospective study.

#### Rationale for secondary aim 1

Bacterial and fungal infections and sepsis are well-known complications in children undergoing intensive chemotherapy. Presence of CVL increases the risk of infections [17-19,41-43]. Two recent prospective studies conducted in children with cancer and hematological disorders reported infection rates of 0.87 and 1.7/1000 catheter-days [18,19]. In one study, 40% of patients had CVL-related infections and 44% of the episodes required CVL removal [43].

Although the association of CVL with infections has been well documented, only recently investigators have begun to explore the correlation of CVL-related infection with underlying local TE [42,43]. Prospective studies conducted in adult patients have shown that the local or systemic CVL-related infections are likely to increase the risk of TE in patients on therapy for cancer [42,43]. A retrospective study showed increased risk of thrombosis in children with cancer and documented infection [odds ratio (OR) 2.2, p = 0.016] [17]. So far there is no prospective study to evaluate the relationship of TE and infection in children with cancer.

#### Rationale for secondary aim 2

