For regression models, we will report the OR (for logistic regression), corresponding standard error, 95% confidence intervals and associated p-values. We will report P-values to 3 decimal places with p-values less than 0.001 reported as p<0.001. For all tests, we will use alpha =0.05 level of significance. Examination of residuals will provide an assessment of model assumptions for regression analyses. Goodnees-of-fit for the models will be performed using appropriate Hosmer-Lemeshov tests. For multivariable regression analysis, we anticipate multicolinearity [54]. We will assess colinearity using the variance inflation factor (VIF) which measures the extent to which the variance of the model coefficients will be inflated (because of the correlation of the variable with other predictor variables) if that variable is included in the model. Variables with VIF >10 will be considered colinear and will be excluded from the analysis [55].

The discriminant performance of the model will be evaluated using sensitivity, specificity and the area under the ROC – receiver operating characteristic curve. We will use bootstrapping approach to internally validate the model. We will compare the performance characteristics (i.e. sensitivity, specificity, area under the ROC curve, etc) between the original model and the bootstrap model. OS and EFS will be estimated using Cox-regression which will allow for adjustment of confounding variables. Hazard ratio (HR) will be calculated using log-rank method.

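### The Discussion moves from a confirmed association straight to predictive use, while the planned discrimination measures describe the multivariable model and not CVL-dysfunction itself

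*Protocol article*

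**What the plan says.** - **Hypothesis.** Protocol article, Primary hypothesis and Primary aim: children with dysfunction are expected to have a higher risk of symptomatic TE, and the risks with and without dysfunction are to be compared.
- **Step to use.** Discussion: "If we confirm our primary hypothesis then we can use CVL-dysfunction as a predictor of TE and will be able to identify children at high" (meaning high risk of TE). The next sentence gives the purpose: designing studies of earlier diagnosis and a randomised trial of prophylaxis.
- **Role of the marker.** Rationale for primary aim: "we propose that CVL-dysfunction may be a good predictor of underlying TE". The same paragraph wants a predictor that reliably picks out patients with a high probability of TE, and names confirming the presence and strength of the association as the first step.
- **Planned measures.** Analysis plan: "The discriminant performance of the model will be evaluated using sensitivity, specificity and the area under the ROC" curve, with bootstrap validation. The candidate factors are age, cancer type, dysfunction, infection and CVL type. Dysfunction is coded presence/absence. Regression output is odds ratios, standard errors, confidence intervals and p-values.
- **Planning figures.** Sample size: "the overall prevalence of TE was 11%; 23% of exposed and 9% of unexposed patients had TE" in retrospective data. The study has 450 patients, 90 exposed and 360 unexposed, with about 50 events.
- **Outcome.** Dependent variables: symptomatic TE only, with no screening for asymptomatic TE. The Strengths and potential limitations section names this as the main limitation.

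**The concern.** A marker can be clearly associated with an outcome and still separate cases from non-cases poorly. The Discussion makes confirmation of the hypothesis the only stated condition for treating dysfunction as a predictor, so the study could meet that condition while the marker discriminates weakly.

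The planned discrimination measures would not settle this, because they belong to a model with several other candidate factors. A good ROC area for that model does not say how much dysfunction contributes. No measure of its added contribution is named.

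The target also shifts. The Rationale for primary aim speaks of underlying TE, but the outcome is symptomatic TE. The same section cites a study that "showed that only 5 of 21 children with CVL-related TE were symptomatic". Accuracy for underlying TE therefore cannot be obtained from this design.

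At stake is which children enter the follow-on studies. The Discussion itself says that prophylaxis has to be weighed against a 5–15% bleeding risk.

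**Working it through.** **1. The plan's own figure.** 450 × 0.11 = 49.5, which reproduces the stated ~50 events. With five predictors this is 50/5 = 10 events per predictor.

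**2. Expected table** from the Sample size section (90 exposed at 23%, 360 unexposed at 9%):

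| | TE | No TE | Total |
|---|---|---|---|
| Dysfunction | 90 × 0.23 = 20.7 | 69.3 | 90 |
| No dysfunction | 360 × 0.09 = 32.4 | 327.6 | 360 |
| Total | 53.1 | 396.9 | 450 |

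The stratum rates imply 53.1 events (11.8%), slightly more than the stated ~50. Step 5 allows for this.

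**3. Association.** Odds ratio = (0.23/0.77)/(0.09/0.91) = 3.02. Power for the unadjusted comparison, assuming a two-sided 0.05 test (the protocol gives alpha but not the sidedness):
- standard error under the null = √[0.118 × 0.882 × (1/90 + 1/360)] = 0.0380
- standard error under the alternative = √(0.23 × 0.77/90 + 0.09 × 0.91/360) = 0.0469
- z = (0.14 − 1.96 × 0.0380)/0.0469 = 1.40, so power is about 92%

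At these rates the hypothesis would probably be confirmed.

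**4. Discrimination of dysfunction alone.**
- Sensitivity = 20.7/53.1 = 39.0% (Wilson 95% interval about 28–53%, using 21 of 53)
- TE without dysfunction = 32.4/53.1 = 61.0%
- Specificity = 327.6/396.9 = 82.5%
- ROC area of a yes/no marker = (0.390 + 0.825)/2 = 0.61
- Positive predictive value = 23% (about 16–33%, using 21 of 90); negative predictive value = 91%

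**5. How far the 61% depends on its inputs.**

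| Reading | TE without dysfunction |
|---|---|
| 23% and 9% varied within rounding | 59–63% |
| 50 events, 20.7 of them exposed | 1 − 20.7/50 = 59% |
| 50 events, 32.4 of them unexposed | 32.4/50 = 65% |
| 11%, 23% and 9% all exact: exposure = (0.11 − 0.09)/(0.23 − 0.09) = 14.3% | 1 − 0.143 × 0.23/0.11 = 70% |
| Exposure 25% | 54% |
| Exposure 39% (top of the paediatric range in Significance of CVL dysfunction) | 0.0549/(0.0897 + 0.0549) = 38% |

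Higher exposure raises sensitivity but lowers specificity. At 39% exposure, sensitivity is 62% and specificity is 0.5551/(0.5551 + 0.3003) = 65%, so the ROC area is (0.620 + 0.649)/2 = 0.63. At 14.3% exposure, sensitivity is 30% and specificity is 0.780/0.890 = 88%, so the area is 0.59. Overall discrimination therefore changes little even though the missed share moves a lot.

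**6. Underlying TE.** In the cited study 16 of 21 CVL-related TE were not symptomatic. That is one study and CVL-related TE only, whereas the outcome here is symptomatic TE at any site. It shows that the two targets can differ widely. It does not quantify the difference for this cohort.

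**The case against.** Several counterarguments have force.

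- **No adoption is planned.** A reader might infer that dysfunction will enter practice once the odds ratio is significant. The documents do not support this: the next sentence of the Discussion concerns future studies and a randomised trial, and the Rationale is conditional and mentions strength as well as presence of association. This stands. It does not remove the gap, because choosing children for those studies also depends on how the marker performs.
- **Predictive values are nearly there.** A reader might infer that they are absent from the plan. In substance the Primary aim compares them: risk in the exposed is the positive predictive value, and one minus risk in the unexposed is the negative one. This stands, although the Analysis plan names only odds ratios as regression output. Sensitivity and specificity of dysfunction could also be read from the same table, so nothing is impossible to compute.
- **Absolute risk matters more than sensitivity for a high-risk group.** Fair: 23% against 9% is what defines such a group, and missing other cases does not lower risk within it. Low sensitivity counts most where dysfunction serves as a surrogate screen, as the Rationale describes.
- **The lack of screening is disclosed.** It is, as the main limitation. That passage does not withdraw the wording about underlying TE.
- **Detail belongs in an analysis plan.** A probability cut-off for the model does, and its absence is not held against the article. The inference stated in the Discussion and the object that is evaluated are both fixed in this document.

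**Conclusion.** The concern holds in limited form. The conclusion that dysfunction can be used as a predictor does not follow from a confirmed association alone, and the planned discrimination measures do not describe dysfunction itself. At the planning figures an odds ratio of about 3.0 coexists with sensitivity about 39%, ROC area about 0.61 and positive predictive value 23%.

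A reader might take the 61% of TE without dysfunction as a fixed property of the marker. It is not. It assumes 20% exposure, which the protocol gives as a minimum, and stratum rates from retrospective data that are given for TE without the word symptomatic. It ranges over 59–70% across readings of the Sample size section and drops to about 38% at 39% exposure. The ROC area stays near 0.6 at the exposure shares checked (14.3%, 20% and 39%).

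Nor do the figures show that dysfunction is useless, or that the primary association analysis is wrong. What is affected is the conclusion drawn from it.

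**What to change.** 1. **Analysis plan.** Add, with 95% confidence intervals, the sensitivity, specificity and absolute risks (positive and negative predictive value) for dysfunction alone, and the gain in ROC area when dysfunction is added to the other predictors. Count only dysfunction dated before the TE, because the presence/absence coding can include dysfunction that arose afterwards. State the period over which dysfunction counts in children without TE, since they have longer to acquire it.
2. **Discussion.** Rest the predictor conclusion on these figures as well as on the odds ratio.
3. **Rationale for primary aim and Discussion.** Limit the claim to prediction of later symptomatic TE. State that accuracy for underlying or asymptomatic TE is not estimated, in line with the limitation already acknowledged.

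The cost is a little extra analysis of data already being collected, and a stated conclusion that may be less favourable. Sample size and the primary association analysis do not change.

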### Strengths and potential limitations of the study

The major strength of the study is the use of a prospective cohort design. Previous studies were single institution studies using retrospective design [17,32,33,36]. These studies report up to 30% of missing data [17,32,33,36]. To avoid this problem we will use uniform data collection forms for all study participants and for patients with TE which is likely to capture all the relevant information. Further, the CVL access data will be collected prospectively and hence the exposure criteria will be recorded properly avoiding any recall bias.

Unlike previous studies, evaluation of CVL-dysfunction is the primary aim of our study which formed the basis of our sample size calculation. By inclusion of only symptomatic and objectively confirmed TE, we will avoid ambiguity over diagnosis, and thus, reporting of TE. Uniform guidelines for diagnosis and evaluation will likely minimize chances of misdiagnosis of TE.

In addition the following steps are taken to minimize sources of errors and likely biases improving internal validity of the study. To avoid selection bias all consecutive newly diagnosed non-CNS cancer patients meeting the inclusion criteria will be eligible and approached for participation in the proposed study. All reported events of TE will be confirmed by an independent adjudication committee. To avoid recall bias CVL access data will be collected prospectively and hence the exposure criteria will be recorded properly. Assessors (radiologists) evaluating for TE will be blinded as regards the “exposure” status to avoid measurement bias. With the use of uniform data collection forms for all study participants and patients with TE, infection and CVL dysfunction, all the relevant information is likely to be captured. Further, all data will be analyzed centrally.

Another strength of the study is that this study is conducted across five pediatric oncology institutions with inclusion of wide range of cancer diagnoses. Hence we think that the findings of the study will be generalizable to pediatric oncology population. The results of this study will also be applicable for adults with cancer as well as to the population of patients with other chronic diseases who need long term CVL.

The main limitation is that we will not be screening for asymptomatic TE. However, the significance of asymptomatic TE detected by screening method is unknown. In addition, children with cancer have an increased risk of TE throughout the cancer-therapy making it difficult to choose an ideal time for screening [17,27,31,36]. The large amount of data collection could be perceived as a limitation of this study. However, this will allow us to evaluate various variables.

In summary, use of CVL has improved the quality of life and care in children with cancer. However, CVL is associated with significant complications namely CVL-dysfunction, TE and infection. This study aims to identify the relationship of these three CVL-related complications and evaluates the role of CVL-dysfunction as a predictor of TE in children with cancer. This study will also prospectively evaluate the impact of CVL-dysfunction on the outcome from cancer. The results of this study in turn will help to identify children at high risk for TE and to develop preventive strategies for both infection and thrombosis. This, we believe, will improve overall outcome of children with cancer.
